**PART THREE: SUBGROUP ANALYSES**

Subgroup analyses will be undertaken by:

- Type of hypertensive disorder (chronic hypertension, gestational hypertension, and preeclampsia).
- Per-protocol and complete case analyses.
- Timing of randomization (11+0 – 19+6; 20+0 – 27+6; 28+0 – 36+0).
- Timing of birth (≤34 weeks’ gestation; >34 weeks’ gestation).

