**ANTICIPATED SAMPLE SIZE**

Our sample will comprise all women with hypertensive disorders of pregnancy (chronic hypertension, gestational hypertension, or preeclampsia) who birthed in Victoria between 2009 – 2020, and were prescribed either labetalol or nifedipine between 11-36 weeks’ gestation. In a blinded review of our data, we have determined our sample size to be approximately 7,500. Of these, approximately 90% received labetalol, and the remaining 10% received nifedipine. Based on this, we are powered to detect an exact difference between groups of ≥3.0% for the maternal primary outcome and ≥5.6% for the neonatal primary outcome.

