**Target Trial Emulation**

| **(A) Research Question** | ***What is the causal effect of exposure to nifedipine on adverse maternal and neonatal outcomes, compared with exposure to labetalol?*** | |
| --- | --- | --- |
|  | **Target Trial (Giant PANDA)** | **Emulation** |
| **(B) Populations** | All women with hypertensive disorders of pregnancy (chronic hypertension, gestational hypertension, or preeclampsia) requiring antihypertensive medication at gestational age 11^+0^-19^+6^; 20^+0^-27^+6^; and 28^+0^-36^+6^.  *Exclusions:* contraindication to labetalol or nifedipine; on both labetalol and nifedipine prior to randomization; unable to provide informed consent; unable to be randomized. | All women with hypertensive disorders of pregnancy (gestational hypertension, chronic hypertension, or preeclampsia) requiring antihypertensive treatment (dispensed labetalol or nifedipine) between 11^+0^ and 36^+6^ weeks’ gestation.  *Exclusions:* Taking both labetalol and nifedipine prior to 11 weeks’ gestation. |
| **(C) Treatment strategies** | Primary  Intention-to-treat (ITT): All women randomized to labetalol or nifedipine, regardless of discontinuation or crossover of treatment groups.    Sensitivity  Per-protocol: All women randomized to labetalol or nifedipine, who continued with assigned treatment until no longer indicated.  On-treatment: All women randomized to labetalol or nifedipine, who continued with assigned treatment until no longer indicated and who self-reported ≥90% adherence across all study contacts. | Primary  Intention-to-treat (ITT): All women who received ≥1 prescription and dispensation of labetalol or nifedipine, including those who received both medications during the study period (crossover will be determined by timing of dispensation) and those who discontinued treatment.  *Crossover defined as receiving both labetalol and nifedipine between 11-36 weeks’ gestation.*  Sensitivity  Per-protocol: All women who received ≥1 prescription and dispensation of labetalol or nifedipine during the study period, but did not receive both medications at any time. |
| **(C) Assignment procedures** | Randomized at diagnosis of hypertension requiring medical intervention (1:1 ratio of nifedipine/labetalol). | “Randomized” (via inverse probability weighting) at point of first dispensation of labetalol or nifedipine during the study period (≥11 weeks’ gestation and ≤36+6 weeks’ gestation). |

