| **(D) Follow-up period** | From 11 weeks’ gestation until 28 days post-birth. | From 11 weeks’ gestation until 28 days post-birth. |
| **(E) Outcomes** | **Primary Maternal**  Severe hypertension (systolic blood pressure ≥160mmHg).  **Primary Neonatal**  Composite of stillbirth, neonatal death (until 28 days post-birth), and NICU admission requiring separation of infant and mother (until 28 days post-birth).  **Secondary Maternal**  *Note: Variables denoted with a * are reported with treatment effect and 95% CI, all others are exploratory only and described with summary statistics*.   - Mean antenatal systolic blood pressure* - New diagnosis of preeclampsia* - Severe maternal morbidity (fullPIERS consensus definition)* - Discontinuation of allocated antihypertensive* - Undesirable effects of allocated antihypertensive* - Maternal death* - Indicated birth (induction of PROM)* - Mean antenatal diastolic blood pressure - Proportion of days with antenatal systolic blood pressure ≥140mmHg - Proportion of days with antenatal diastolic blood pressure ≥90mmHg - Diagnosis of eclampsia - Diagnosis of HELLP syndrome - Placental abruption - Components of severe maternal morbidity - Maternal stroke - Prescription of additional antihypertensive drugs - Prescription of alternative antihypertensive drugs - Time from randomization to first discontinuation of allocated antihypertensive - Total number of antenatal hospital inpatient days - Treatment satisfaction - Beliefs about allocated antihypertensive drug - Adherence to allocated antihypertensive drug - Mode of onset of birth   **Secondary Neonatal**  *Note: Variables denoted with a * are reported with treatment effect and 95% CI, all others are exploratory only and described with summary statistics*.   - Major congenital anomaly (as defined by EURO-CAT)* - Birthweight centile* - Need for treatment for neonatal hypoglycemia* - Neonatal unit admission (separation of baby from mother)* - Mode of birth* - Gestational age at birth* - Fetal loss <24^+0^ weeks’ gestation - Fetal loss ≥24^+0^ weeks’ gestation (stillbirth) - Known early neonatal death (up to 7 days post-birth) - Known late neonatal death (7-28 days post-birth) - Principal recorded indication for neonatal unit admission - Length of stay in neonatal unit (and level of care) - Indication for mode of birth - Preterm birth (<37 completed weeks) - Preterm birth (<32 completed weeks) - Birthweight - Birthweight SGA (<10^th^ centile) - Umbilical arterial pH<7 at birth - Apgar score 5min post-delivery - Need for additional resuscitation at birth - Need for respiratory support - Type of respiratory support needed - Type of treatment for hypoglycemia - Lowest blood glucose measurement within 48 hours post-birth - Intracranial hemorrhage - Neonatal seizures - Necrotizing enterocolitis | **Primary Maternal**  Our primary outcome will be a composite of severe maternal morbidity determined by an expert panel, comprising:   - Maternal mortality (all cause) - Eclampsia - HELLP syndrome - Stroke - Cortical blindness - Retinal detachment - Pulmonary oedema - Placental abruption - Liver rupture - Need for dialysis - Need for extracorporeal membrane oxygenation (ECMO)   *Note: We do not have reliable ascertainment of ICU/HDU admission data. By instead including only severe morbidities which can reasonably be attributed to hypertensive disorders, we will provide a more accurate picture of the effect of disease-modifying drugs.*  **Primary Perinatal**  Our primary perinatal outcome will be a composite outcome determined by expert consensus. This will comprise.   - Stillbirth (fetal death ≥20 weeks’ gestation) - Neonatal death (death within 28 days of birth) - Severe neonatal morbidity, including:   - Bacterial sepsis   - Birthweight < 3^rd^ centile   - Cardiac arrest   - Hypoxic-ischemic encephalopathy (HIE)   - Intracranial hemorrhage   - Necrotizing enterocolitis   - Neonatal asphyxia   - Neonatal seizures   - Requirement for intubation or mechanical ventilation   - Requirement for resuscitation (mechanical or non-mechanical)   *Note: We do not have reliable ascertainment of NICU admission data. Many infants who are born following hypertensive pregnancies will be admitted to NICU without any other severe morbidities. By instead including only diagnosed severe morbidities, we will provide a more accurate picture of the effect of disease-modifying drugs.*  **Secondary Maternal**  *Note: Variables denoted with a * are reported with treatment effect and 95% CI, all others are exploratory only and described with summary statistics*.   - Pregnancy prolongation (time from first antihypertensive dispensation to birth)* - Need for additional antihypertensive(s)* - Individual components of the primary composite outcome - Disease progression (new diagnosis of preeclampsia after randomization)   **Secondary Perinatal**  *Note: Variables denoted with a * are reported with treatment effect and 95% CI, all others are exploratory only and described with summary statistics*. *** Indicates core secondary outcome.*   - Preterm birth (<37; <34; <32; and <28 weeks’ gestation)** - Major congenital anomaly (as defined by EURO-CAT)* - Neonatal hypoglycemia* - Respiratory distress - Neonatal hypothermia - Individual components of primary composite outcome - Birthweight <10^th^ centile |

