**Developing a causal model using directed acyclic graphs (DAGs) to both identify and summarise causal pathways.**

1. Potential confounders will be determined by the above-named authorship team (a quorum of specialists with expert knowledge). All potential confounders are pre-exposure or at exposure.
   1. Covariates to be included in the selection model:
      1. Type of hypertension (gestational hypertension, chronic hypertension, preeclampsia)*
      2. Maternal diabetes mellitus (yes/no)*
      3. Plurality (1/2+)*
      4. Pre-existing renal disease
      5. Pre-existing autoimmune disease
      6. Maternal smoking during pregnancy
      7. Maternal body mass index
      8. IVF/ART conception
      9. Maternal socioeconomic status (SEIFA quintile)
      10. Maternal age at delivery
      11. Mode of birth (neonatal outcomes only)

*Variables denoted with * are included in the Giant PANDA randomization algorithm.*

**Causal pathway and confounding** (excerpt from Causal Inference, What if. M Hernan & J Robins p85: <https://www.hsph.harvard.edu/miguel-hernan/causal-inference-book/>)

*“...the bias has the same structure: it is due to the presence of a cause (known covariate L or unknown covariate U) that is shared by the treatment A and the outcome Y, which results in an open backdoor path between A and Y. We refer to the bias caused by shared causes of treatment and outcome as confounding…”*

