3. Total number of dose(s) of allocated antihypertensive drug (mean, SD)
4. In the target trial, there were several **secondary perinatal outcomes** (see *Target Trial Emulation* Table Sfor full list). In our emulation, we will report the following secondary outcomes with treatment effect and 95% confidence intervals (CI):
   1. Preterm birth <37; <34; <32; and <28 weeks’ gestation (yes/no)
   2. Birthweight ≤3^rd^ centile (yes/no)
   3. Neonatal hypoglycemia (yes/no)
   4. Major congenital anomaly as defined by EURO-CAT (yes/no)

Additionally, the following outcomes will also be reported in an exploratory capacity (i.e., with summary statistics only):

1. Individual components of the primary composite outcome (all yes/no)
2. Birthweight <10^th^ centile (yes/no)
3. Mode of birth (spontaneous vaginal, operative vaginal, elective caesarean section, emergency caesarean section)

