**Causal contrasts of interest**

1. **Estimand**

**Maternal outcomes** – relative risk (RR) and risk difference (RD) of primary composite outcome and pre-specified (*) secondary outcomes (ATE RR, 95% CI).

**Neonatal outcomes** – relative risk (RR) and risk difference (RD) of primary composite outcome and pre-specified (*) secondary outcomes (ATE RR, 95% CI).

In the Giant PANDA RCT, the primary neonatal binary outcome is estimated using a type of logistic regression (log-binomial) model. We will use a logistic regression model with robust standard errors (to adjust for maternal clustering). This model provides predictive probabilities that are then used to calculate both the between exposure difference (RD) and relative risk (RR) for all binary and highlighted (*) secondary outcomes.

In our emulated target trial, the estimand is the average treatment effect (ATE) between exposures, presented using both RD and RR metrics. Within the potential outcomes framework, a causal interpretation can be made under the assumptions of counterfactual consistency, ignorability (conditional exchangeability), and positivity. Counterfactual consistency means that the definition of exposure is consistent for all individuals. Ignorability states that treatment assignment can be considered exchangeable (i.e. as if the assignment was randomized) after controlling for, or conditioning on, a set of covariates. This implies that there are no important unmeasured confounders, an untestable assertion. The positivity assumption means that, for all observations, the conditional probability of being exposed and of not being exposed (receiving treatment or not receiving treatment) are both greater than zero.

1. **Estimators**

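### The timing-of-birth subgroup splits on something treatment can change, so its drug comparisons have no causal reading and can be biased in both strata

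*SAP*

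**What the plan says.** Part Three (Subgroup Analyses) lists "Timing of birth (≤34 weeks’ gestation; >34 weeks’ gestation" next to type of hypertensive disorder and timing of randomization. It gives no caveat, no descriptive-only label and no separate estimand.

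The Target Trial Emulation table places assignment "at point of first dispensation of labetalol or nifedipine during the study period (≥11 weeks’ gestation and ≤36+6 weeks’ gestation". Birth therefore always follows time zero.

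The SAP also treats birth timing as a result of treatment, in two places:

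- The outcome definitions include, among the secondary perinatal outcomes to be reported with a treatment effect and 95% CI, "Preterm birth <37; <34; <32; and <28 weeks’ gestation (yes/no".
- The Target Trial Emulation table stars, among the secondary maternal outcomes, "Pregnancy prolongation (time from first antihypertensive dispensation to birth".

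For adjustment variables the SAP sets its own standard: "All potential confounders are pre-exposure or at exposure". Under Causal Contrasts of Interest the estimand is the average treatment effect, and its causal reading rests on exchangeability given covariates: "Ignorability states that treatment assignment can be considered exchangeable".

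**The concern.** A subgroup that is to carry a treatment effect has to be defined at or before assignment. Gestation at birth is not. Essentially the same 34-week boundary (≤34 in the subgroup, <34 in the outcome) serves both as an outcome of treatment and as the stratifier within which treatment is compared.

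Birth timing has at least two causes here: possibly the drug, and certainly disease severity. The SAP states that it has no reliable blood pressure measurements, and its covariate list contains none, so part of severity stays unmeasured. Conditioning on a common effect of drug and severity links the two within each stratum, even when they are independent overall. If one drug delays birth, the women on that drug who still deliver early are a sicker selection than their comparators. The women on that drug who deliver later include some sicker women who would otherwise have delivered early. Both strata are then tilted against that drug.

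Because both strata move the same way, a reader could take them as consistent harm (or benefit) where there is none. That is a poor result for a plan whose purpose is causal inference to inform practice.

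**Working it through.** The SAP states no figure on this point, so there is none to reproduce. The check is whether a null drug effect on morbidity can appear non-null in both strata.

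**Illustration 1, continuous severity (all inputs assumed).** U ~ N(0,1) is unmeasured severity. A = 1 is the exposed drug, fully exchangeable. T is birth at or before 34 weeks. Y is the morbidity outcome.

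- logit P(T=1) = −1.7 + 1.2U + bA, with b = −0.6 (odds ratio exp(−0.6) = 0.55)
- logit P(Y=1) = −3.0 + 1.0U, with no term in A, so the true risk ratio is 1.00 for every woman

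The stratum risk is P(Y | A, T=t) = E[P(Y|U) P(T=t|A,U)] / E[P(T=t|A,U)], with expectations over U. Exact integration gives:

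| | A=1 | A=0 | Ratio |
|---|---|---|---|
| P(birth ≤34 weeks) | 13.6% | 20.7% | – |
| Mean U, ≤34 stratum | 0.88 | 0.78 | – |
| Mean U, >34 stratum | −0.14 | −0.20 | – |
| Risk of Y, ≤34 stratum | 13.58% | 12.48% | 1.09 |
| Risk of Y, >34 stratum | 5.88% | 5.49% | 1.07 |
| Risk of Y, all women | 6.93% | 6.93% | 1.00 |

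The mean of U shows the mechanism: in both strata the A=1 women are sicker. A simulation of 4 million records with 10% exposed gave 1.095 and 1.071, so its early-stratum value differs from the exact 1.089 only by Monte Carlo error.

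Varying the effect on timing in the same model:

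| b (odds ratio on timing) | RR, ≤34 | RR, >34 |
|---|---|---|
| −0.6 (0.55) | 1.09 | 1.07 |
| −0.2 (0.82) | 1.03 | 1.03 |
| −0.1 (0.90) | 1.01 | 1.01 |
| 0 (1.00) | 1.00 | 1.00 |
| +0.6 (1.82) | 0.91 | 0.92 |

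**Illustration 2, binary severity (all inputs assumed).** Severity prevalence is 0.3, its odds ratio with Y is 5 and with early birth 3 to 6; baseline logits are −1.7 (early birth) and −3.2 (Y). The true RR is again 1.00. Exact results, as ranges over the severity–timing odds ratio:

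| Drug–timing odds ratio | RR, ≤34 | RR, >34 |
|---|---|---|
| 0.5 | 1.04 to 1.06 | 1.04 to 1.08 |
| 0.7 | 1.02 to 1.03 | 1.02 to 1.04 |
| 1.0 | 1.00 | 1.00 |
| 1.5 | 0.97 to 0.96 | 0.97 to 0.95 |
| 2.0 | 0.95 to 0.92 | 0.95 to 0.92 |

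**Size against sampling error.** The SAP expects about 7,500 women, of whom "approximately 90% received labetalol, and the remaining 10% received nifedipine", that is about 6,750 and 750. Under illustration 1 with b = −0.6:

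- The early stratum has 750 × 0.1363 ≈ 102 exposed and 6,750 × 0.2066 ≈ 1,394 comparators. With SE(log RR) = √[(1−p₁)/(n₁p₁) + (1−p₀)/(n₀p₀)] = 0.259, the unweighted 95% interval around 1.09 is 0.65 to 1.81.
- The later stratum has about 648 and 5,356 women. The SE is 0.167, and the interval around 1.07 is 0.77 to 1.49.

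**The case against.** Several fair points can be made for leaving the subgroup in.

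- **The bias is conditional.** It needs the drugs to differ in their effect on birth by 34 weeks, and an unadjusted cause of both timing and outcome. Both arms are active antihypertensives, and the SAP offers no evidence that they differ. This stands as a limit on size, and the tables show the bias vanishing at an odds ratio of 1. It does not rescue the split: whether the drugs differ on timing is what the SAP's own secondary outcomes set out to test, so it cannot be assumed in order to justify the stratification.
- **The assumed timing effect is large, and the bias is small against the intervals above.** True. But wide intervals do not make an estimate valid, and the two strata err in the same direction.
- **The illustrations give morbidity no dependence on gestation at birth.** That is a strong simplification for the perinatal composite, which includes conditions such as necrotizing enterocolitis and intracranial hemorrhage. The figures should not be carried over to that outcome.
- **Women first dispensed after 34 weeks can only fall in the later stratum, but that alone does not bias the comparison between drugs.** Correct, unless drug choice varies with gestation. It does mean that the split mixes timing of assignment with an outcome. Gestation at first dispensation is in neither the covariate list nor the balance tables.
- **Removing a prespecified analysis late could look selective.** The document already reports balance results for both primary models, so this deserves care. It bears on how the change is recorded, not on whether the split is sound.

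**Conclusion.** The point holds. The subgroup conditions on a post-assignment variable that the SAP elsewhere analyses as an outcome, and baseline weighting cannot restore exchangeability within its strata. With a true risk ratio of 1.00, the spurious stratum ratios ran from about 0.91 to 1.09 over the assumed inputs, with both strata displaced in the same direction. The size and sign in the real data depend on the drugs' relative effect on timing and on the strength of unmeasured severity, neither of which the SAP gives, so these figures are illustrations and not estimates. The consequence is confined to this subgroup; the primary average treatment effect does not use the split. It should be corrected, but it does not threaten the main result.

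**What to change.** Delete the timing-of-birth line from Part Three. Use timing of first dispensation, already listed there, as the gestation subgroup, since it is known at time zero. Its last band is written as ending at 36+0 while eligibility runs to 36+6, so the two should be aligned in the same edit.

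If birth timing is of interest, define a joint outcome in the full weighted population, for example the composite event together with birth at or before 34 weeks. State that such a contrast includes any effect on timing. In illustration 1 the joint risks are 0.1363 × 0.1358 = 1.85% and 0.2066 × 0.1248 = 2.58%, a ratio of 0.72 that comes wholly from delayed birth. Preterm birth below 34 weeks is already reported as an outcome.

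If results by birth timing have already been produced, record the deletion with its reason and date. Should the team still wish to show them, present event counts by drug, labelled descriptive and non-causal, without a treatment-effect estimate.

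The cost is one line of the SAP and one fewer analysis. No new data are needed.

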**SOFTWARE**

Analysis will be performed using Stata v18 (StataCorp. 2023. *Stata Statistical Software: Release 18*. College Station, TX: StataCorp LLC). Causal inference will be performed using *teffects* commands (treatment-effects estimation for observational data, see TE-teffects) run within Stata’s multiple imputation suite and TMLE using the *etmle* module^9^ or *TMLE* package in R.

**Direct Acyclic Graphs (DAGs) for primary analyses**

[figure not shown]

[figure not shown]

1. Direct Acyclic Graph (DAG) for maternal primary composite outcome

[figure not shown]

[figure not shown]

1. Direct Acyclic Graph (DAG) for neonatal primary composite outcome

**Details of imputation models**

|  | Observations per m | | | |
| --- | --- | --- | --- | --- |
| Variable | Complete | Incomplete | Imputed | Total |
| BMI | 7174 | 371 | 371 | 7545 |
| Smoking | 7471 | 74 | 74 | 7545 |
| SEIFA | 7542 | 3 | 3 | 7545 |
| IVF/ART Conception | 7521 | 24 | 24 | 7545 |
| Birthweight | 7532 | 13 | 13 | 7545 |

Observed raw data

| Variable | N | Mean | SD | Min | Max |
| --- | --- | --- | --- | --- | --- |
| BMI | 7174 | 31.71 | 7.50 | 10.01 | 59.88 |
| Smoking | 7471 | 0.16 | 0.37 | 0 | 1 |
| SEIFA | 7542 | 3.13 | 1.31 | 1 | 5 |
| IVF/ART Conception | 7521 | 0.09 | 0.28 | 0 | 1 |
| Birthweight | 7532 | 2926.36 | 734.23 | 160 | 5860 |

Imputed data bootstrap 1, m=1

| Variable | N | Mean | SD | Min | Max |
| --- | --- | --- | --- | --- | --- |
| BMI | 7545 | 31.69 | 7.49 | 10.01 | 59.88 |
| Smoking | 7545 | 0.16 | 0.37 | 0 | 1 |
| SEIFA | 7545 | 3.13 | 1.31 | 1 | 5 |
| IVF/ART Conception | 7545 | 0.09 | 0.28 | 0 | 1 |
| Birthweight | 7545 | 2922.03 | 741.39 | 160 | 5860 |

Imputed data bootstrap 2, m=2

| Variable | N | Mean | SD | Min | Max |
| --- | --- | --- | --- | --- | --- |
| BMI | 7545 | 31.69 | 7.51 | 10.01 | 59.88 |
| Smoking | 7545 | 0.17 | 0.37 | 0 | 1 |
| SEIFA | 7545 | 3.13 | 1.31 | 1 | 5 |
| IVF/ART Conception | 7545 | 0.09 | 0.28 | 0 | 1 |
| Birthweight | 7545 | 2922.11 | 741.21 | 160 | 5860 |

Proportions for SEIFA (m=1)

| **SEIFA Quintile** | **Observed** | **Imputed** | **Completed** |
| --- | --- | --- | --- |
| 1 | 0.154 | 0.333 | 0.154 |
| 2 | 0.163 | 0.333 | 0.163 |
| 3 | 0.266 | 0.000 | 0.265 |
| 4 | 0.237 | 0.000 | 0.237 |
| 5 | 0.180 | 0.333 | 0.180 |

Proportions for smoking status (m=1)

| **Smoking Status** | **Observed** | **Imputed** | **Completed** |
| --- | --- | --- | --- |
| Yes | 0.165 | 0.122 | 0.164 |
| No | 0.835 | 0.878 | 0.836 |

Proportions for IVF/ART conception (m=1)

| **IVF/ART Conception** | **Observed** | **Imputed** | **Completed** |
| --- | --- | --- | --- |
| Yes | 0.087 | 0.208 | 0.088 |
| No | 0.913 | 0.792 | 0.912 |

Proportions for BMI (m=1)

[figure not shown]

Proportions for birthweight (m=1)

[figure not shown]

